**vii) Study interventions**

In this study, two interventions will be provided: i) intermittent screening and treatment (IST) for malaria and ii) a programme of training for primary school teachers to improve literacy instruction.

The malaria prevention strategy will involve all children being screened using rapid diagnostic tests (RDTs) for malaria once a term (thrice yearly). Children (with or without malaria symptoms) found

to be RDT-positive will be treated with artemisinin-based combination therapy (ACT). Screening and treatment will be administered by district health workers once a school term, observed by the evaluation research team.

An education intervention will be conducted in half of the schools receiving IST and half of the control schools. The intervention is designed to improved early grade literacy instruction. Recent evidence (Snow et al., 1998) suggests that relatively simple steps can be taken by teachers in order to improve the development of children's literacy in the early grades. It is particularly important to develop students' oral language skills (e.g., phonological awareness & vocabulary) and to teach the relationship between letters and sounds in a systematic and explicit fashion. Such instructional techniques are encouraged in the current Kenyan curriculum but teachers face many challenges in implementing them systematically and effectively. The aim of the instructional intervention will be to support teachers in implementing these teaching methods. Specific interventions will be design based on further consultation with all stakeholders and ongoing class observations in Kwale but may include training on (i) how to monitor students' progress in large classes (ii) developing and using instructional materials for reading (iii) lesson planning for explicit teaching of letter-sound relationships (iv) instructional techniques for large classes.

### **viii) Survey investigations**

Survey tools and procedures have been used previously to estimate the health and educational impact of IPT in Kenyan schoolchildren (Clarke et al., 2008). These standard tools and operating procedures have been adapted based on previous collective experience. These are detailed below and summarized in Table 2.

| Table 2. Outcome measurements      |                 |                    |                    |
|-------------------------------------------|-----------------|--------------------|--------------------|
| Outcome                            | Baseline | Follow-up 1 | Follow-up 2 |
| Consent                                   |                 |                    |                    |
| Hb concentration                          |                 |                    |                    |
| Malaria parasitaemia                      |                 |                    |                    |
| Child literacy and numeracy               |                 |                    |                    |
| School attendance                         |                 |                    |                    |
| Behavioural assessments                   |                 |                    |                    |
| Socio-economic and educational covariates |                 |                    |                    |
| Soil-transmitted helminths                |                 |                    |                    |
| Urinary schistosomiasis                   |                 |                    |                    |

*Seeking consent:* Selected schools will be visited one month prior to the survey date to have the purpose of the survey explained to the head teacher and school committee, and informed parental consent will be sought from the parents/guardians of children. See section 11. Parents of included children will be asked a series of questions including known parental education, known reactions of their children to anti-malarials, and location of household (Appendix 2). This information will used to (i) help trace children absent from school during follow-up and (ii) control for potentially confounding variables in the data analysis.

*Survey procedures:* Seven staff travelling in a single vehicle will visit each school: one supervisor; three laboratory technicians; one laboratory assistant; one nurse; plus one driver. An initial meeting will be held with the head teacher. In order to minimize disruption, one class will be selected at a time. Two education testers will assess cognitive function and educational achievement in the week before the arrival of the health team.

A series of questions will be asked of each randomly selected participating child including: age, fever on the day of the survey, basic household assets indicators, source of potable water in the homestead, use of mosquito nets treated with insecticide (Appendix 3). This information will used to control for potentially confounding variables in the data analysis.

On the day of enrollment to the study, children will have their height measured to the nearest 0.1 cm using a portable fixed base stadiometer and weight measured to the nearest 0.1 kg using an electronic balance.

**No assessment** of malaria parasitaemia and anaemia will be made **at baseline**. However, to measure success of the randomization, children from classes 6 and 7, not enrolled in the study, will be asked to provide a finger-prick blood sample for the preparation of a thick and thin blood smear for malaria investigation. The same finger prick sample will be used at the point of survey to record haemoglobin concentrations using a portable spectrophotometer.

**All enrolled children** in classes 1 to 5 will be asked to provide a finger-prick blood sample at **follow-up** to assess malaria parasitaemia and anaemia.

For those children with a reported fever or a history of fever in the last 48 hours, a drop of blood will be used to perform a rapid malaria test (OptiMal). Any child with a positive test and symptoms will be treated using artemether-lumefantrine (Co-artem) on the day of the survey according to national guidelines or referred to the nearest health facility if necessary. Transportation costs will be provided and an agreement will be reached with facilities to waive appropriate drug costs. Children identified as severely anaemic (haemoglobin levels < 8 g/dL) will receive ferrous sulphate according to national guidelines.

As part of a national school-based deworming, all schools in Kwale district would have received mass treatment for STH infection using albendazole [400mg]. Therefore, no anthelmintic treatment will be provided in the present study. During the final follow-up pots for stool samples will be distributed to all selected children who will be asked to return the following day with a sample. Children will also be asked to provide a urine sample. These results will be used to assess the need for further anthelmintic treatment, in accordance with national guidelines: mass treatment for STH infection using albendazole [400mg] in schools where prevalence exceeds 50%; mass treatment for *S. haematobium* using praziquantel [40 mg/kg] in schools where prevalence exceeds 50%; in remaining schools, only those found to be infected with *S. haematobium* will be treated.

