## 3. Abstract

The Government of Kenya is committed to improving the education of its children, and recognizes the importance of child health for educational achievement. While malaria represents one of the main health problems afflicting Kenyan schoolchildren, the evidence base for policy development and programme implementation for school-based malaria control remains inadequate. A recent study in western Kenya showed that delivering intermittent preventive treatment (IPT) to schoolchildren improved rates of anaemia and classroom concentration, but did not improve school performance. This study aims to (i) investigate the impact of a related malaria prevention strategy, intermittent screening and treatment, on health and education among schoolchildren in a different malaria transmission setting and (ii) determine the interaction between health and improved literacy instruction. The study will be undertaken in 100 randomly selected primary schools in Kwale District. IST will consist of all children being screened using rapid diagnostic tests (RDTs) for malaria once a term (thrice yearly). Children (with or without malaria symptoms) found to be RDT-positive will be treated with artemisinin-based combination therapy (ACT). Screening and treatment will be administered by district health workers. The education intervention will involve a programme of training for primary school teachers to improve literacy instruction. The study is designed to detect a 25% reduction in anaemia and an improvement of 0.2 standard deviations in mathematics and literacy tests. Additional outcomes will also be measured including malaria parasitaemia, classroom attention and school attendance. Health and educational outcomes will be assessed before intervention and twelve and twenty four months later. Information will also be collected on in-vivo parasitological efficacy of treatments and the cost-effectiveness of intervention. The findings of this study will provide critical information on the effectiveness of interventions to reduce the health and education burden of malaria among school-aged children.

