## **ii) Outcome measures**

### **Primary outcomes:**

1. Prevalence of anaemia
2. Education achievement assessed by a battery of tests of reading, writing and arithmetic

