#### **Data analysis**

All analyses will be on the basis of intention-to-treat. To assess the success of randomization baseline characteristics between the four randomization groups will be compared. To assess the impact of the interventions, methods appropriate for cluster-randomized trials will be used (Hayes & Bennett, 1999). The prevalence, or mean, in each school will be calculated and the unadjusted risk ratio (RR), or mean difference (intervention-control), estimated in each stratum. An overall estimate of the effect of IST will be obtained by taking a weighted average of the stratum-specific estimates, the weights proportional to the number of schools per stratum, and 95% confidence intervals will be adjusted for observed between-school variance. Formal hypothesis testing will be undertaken using stratified unpaired t-tests. The impact of each intervention will be estimated for education outcomes and health outcomes in separate multiple regression models. An interaction term will be included to identify any synergistic effects between the two interventions. Statistical analysis will be carried out using STATA® software, version 10.0. (Stata Corporation, Texas, USA).

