### **10. Time Frame**

|                                                        |     |     |     |     |     |     |     |     |     |     |     |     |
|--------------------------------------------------------|-----|-----|-----|-----|-----|-----|-----|-----|-----|-----|-----|-----|
| 2008                                            |     |     |     |     |     |     |     |     |     |     | Nov | Dec |
| Staff recruitment and training                         |     |     |     |     |     |     |     |     |     |     |     |     |
| Development and piloting of education assessment tools |     |     |     |     |     |     |     |     |     |     |     |     |
| 2009                                            | Jan | Feb | Mar | Apr | May | Jun | Jul | Aug | Sep | Oct | Nov | Dec |
| Development and piloting of education assessment tools |     |     |     |     |     |     |     |     |     |     |     |     |
| Teacher training workshop                              |     |     |     |     |     |     |     |     |     |     |     |     |
| Baseline health and education surveys                  |     |     |     |     |     |     |     |     |     |     |     |     |
| IST                                                    |     |     |     |     |     |     |     |     |     |     |     |     |
| Instruction intervention                               |     |     |     |     |     |     |     |     |     |     |     |     |
| Assessment of class behaviour                          |     |     |     |     |     |     |     |     |     |     |     |     |
| 2010                                            | Jan | Feb | Mar | Apr | May | Jun | Jul | Aug | Sep | Oct | Nov | Dec |
| First follow-up health and education surveys           |     |     |     |     |     |     |     |     |     |     |     |     |
| IST                                                    |     |     |     |     |     |     |     |     |     |     |     |     |
| Instruction intervention                               |     |     |     |     |     |     |     |     |     |     |     |     |
| Assessment of class behaviour                          |     |     |     |     |     |     |     |     |     |     |     |     |
| First follow-up health and education surveys           |     |     |     |     |     |     |     |     |     |     |     |     |

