## 11. Ethical considerations

### *Informed consent process*

Prior to the onset of the study, parent-teacher association meetings will be held with the parents/guardians of children enrolled in standards 1-5 to describe the purpose of the study, the procedures to be followed, and the risks and benefits of participation. Information sheets ([Appendix 11](#)) will be provided to the parents or guardians for their review. For those parents who not attend these meetings, follow-up will be made through community leaders and household visits.

The parents or guardians will be asked to sign consent for their child (if aged under 18 years) to participate in the research study ([Appendix 11](#)). If the child is aged 18 years or over, is married or is a mother (so-called emancipated minor by Kenyan law), they will be asked to provide consent themselves. If a parent, guardian or older child is unable to read or write, his/her fingerprint will be used in substitute for a signature, and a signature from a witness to the informed consent discussion will be obtained. Parents and guardians will have the chance to ask questions and will be informed that participation of their child(ren) in the study is completely voluntary and that they may withdraw from the study at any time.

Information about all children, including age, gender, and any history of known allergies or adverse reactions to study medications, will be obtained from parents/guardians and captured on an initial screening form ([Appendix 2](#)). Details about the location of the students' homes will also be obtained from the parent/guardians to facilitate tracing in the event of absence from school on subsequent follow-up visits. A record will be made of those children for whom consent is provided and will be cross-checked against school registers.

Written consent to participate in the stakeholder interviews and focus groups discussions will be sought.

Verbal assent to participate in the study will also be obtained from the child at the time of screening ([Appendix 11](#)).

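### Health outcomes are said to be assessed before intervention, but the cohort has no baseline blood sample; the class 6-7 school values collected instead have a randomisation check as their only stated use, when they could also adjust the anaemia and parasitaemia analyses

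*Protocol*

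**What the plan says.** **Timing of health outcomes.** The Protocol's section 3 (Abstract) states: "Health and educational outcomes will be assessed before intervention and twelve and twenty four months later". Section 8 i) (General Study design) repeats the sentence, and section 10 (Time Frame) has a row for "Baseline health and education surveys".

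Section 8 viii) (Survey investigations) says otherwise. Its sentence on baseline opens with a bolded negative, continues "of malaria parasitaemia and anaemia will be made", and ends by naming baseline. Enrolled children "in classes 1 to 5 will be asked to provide a finger-prick blood sample at" follow-up. The pre-intervention smears and haemoglobin come from other children: "to measure success of the randomization, children from classes 6 and 7, not enrolled in the study".

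**Which outcomes are affected.** The primary health outcome is "Prevalence of anaemia". The secondary one is prevalence of parasitaemia. No other health outcome is listed; height, weight and reported fever are recorded but are not outcomes.

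**Use in the analysis.** Section 9 (Data analysis) says: "To assess the success of randomization baseline characteristics between the four randomization groups will be compared". It then sets an unadjusted risk ratio or mean difference per stratum, a weighted average over strata and stratified unpaired t-tests. Separate multiple regression models follow, with no covariates listed. The strata are examination performance (section 8 vi). Section 8 viii) assigns parent and child questionnaire items to confounder control, but not the class 6-7 blood results.

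**The concern.** A reader of the abstract would expect each enrolled child to have a haemoglobin and parasitaemia result before intervention. On the survey procedures, no such result will exist, so a within-cohort before-and-after comparison of health is not possible.

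The second issue is what happens to the health baseline that is collected. Comparing arms on it can show a chance imbalance but does not correct one. Schools differ considerably: the 2008 survey reports anaemia of 3-37% and malaria of 1-28% by school. Strata based on examination results need not track either. Elsewhere the protocol accepts the value of baseline data. Section 8 v) credits a baseline-to-final correlation of 0.7 for the education tests, and section 8 ix) argues that covariates raise power considerably in school-based cluster trials. It does not carry this over to its anaemia primary outcome.

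**Working it through.** **1. The sections side by side.** Sections 3 and 8 i) give three time points for health outcomes: before intervention, 12 months and 24 months. Section 8 viii) gives enrolled children blood tests at follow-up only. Both cannot be true of the same children. The comparison does not use Table 2, whose cells are blank in the text at hand.

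**2. The plan's own figure.** Inputs from section 8 v): prevalence 20% falling to 15% (a 25% reduction), 80% power, 5% significance (taken as two-sided), 50 children per school, intraclass correlation (ICC) 0.025.

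- Individually randomised sample: 906 per group, or 945 with continuity correction.
- Design effect: 1 + 49 × 0.025 = 2.225.
- Schools per side: 906 × 2.225 / 50 = 40.3, or 945 × 2.225 / 50 = 42.05. The unpooled formula plus one cluster gives 41.2, rounded up to 42.

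So 84 schools reproduce as 42 IST against 42 non-IST schools (power 0.816) without any health covariate. With 50 against 50 schools, power is 0.877.

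**3. Expected chance imbalance.** For 50 against 50 schools at 20% prevalence:

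- SD of the difference in observed prevalence = √(2 × 0.16 × 2.225 / (50 × 50)) = √0.000285 = 0.017, or 1.7 percentage points.
- The between-school part alone: √(2 × 0.004 / 50) = 0.013, or 1.3 points.
- Target difference: 20 − 15 = 5 points.

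**4. What adjustment could gain.** Between-school variance is 0.025 × 0.16 = 0.004. Sampling variance of a school's cohort prevalence is 0.16 / 50 = 0.0032.

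- Reliability of the cohort school value: 0.004 / 0.0072 = 0.556.
- Reliability of the class 6-7 value: 0.004 / (0.004 + 0.16/20) = 0.333 with 20 children, and 0.556 with 50.
- Variance reduction = (true school-level correlation)² × cohort reliability × class 6-7 reliability.

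The protocol states neither the correlation nor the number of class 6-7 children sampled. Both are assumptions:

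| True correlation | 20 children | 50 children |
|---|---|---|
| 0.3 | 0.09 × 0.556 × 0.333 = 1.7% | 0.09 × 0.556 × 0.556 = 2.8% |
| 0.5 | 0.25 × 0.556 × 0.333 = 4.6% | 0.25 × 0.556 × 0.556 = 7.7% |
| 0.9 | 0.81 × 0.556 × 0.333 = 15% | 0.81 × 0.556 × 0.556 = 25% |

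In equivalent schools this is 1 / (1 − 0.017) = 1.02 times the number at the low end and 1 / (1 − 0.25) = 1.33 times at the high end.

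**5. In terms of power.** The adjusted design effect is 0.975 + 1.25 × (1 − r²), where r is the correlation of the observed class 6-7 value with the true cohort school level. Sampling error alone caps r at about 0.58 (20 children) to 0.75 (50 children).

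- Low corner: r = 0.3 × 0.58 = 0.17, design effect 2.19, power about 0.88 with 50 against 50 schools.
- High corner: r = 0.9 × 0.75 = 0.675, design effect 1.66, power about 0.95.

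**The case against.** **On the contradiction.** The abstract and design sentences do not say that the baseline is in the cohort, and the school is the unit of analysis. Smears and haemoglobin from classes 6-7 are a school-level health assessment before intervention, and the survey procedures are explicit about what is done in the field. This makes it a matter of wording. The correction is still needed: one sentence covers all three time points as if they concerned the same children, while the procedures deny a baseline assessment and describe the class 6-7 children as not enrolled.

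**On adjustment.** A reader might infer that nothing in the analysis adjusts for differences between schools. The document does not support that. Section 9 plans regression models for health outcomes, section 8 viii) names questionnaire items for confounder control, and the estimate is weighted over strata meant to reflect school quality and socio-economic environment. A covariate list may properly sit in an analysis plan, and section 8 xii) refers to one. It is not shown and could include the class 6-7 values. What remains is what the protocol itself fixes: an unadjusted effect estimate with stratified t-tests as the formal test, and one stated purpose for the class 6-7 data.

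**On size.** The class 6-7 children are older, are different children, and are measured 12 to 24 months before the follow-ups, so the correlation may be low and the gain near 2%. Strata and other covariates may already explain part of the same variance. The 2008 school ranges include sampling error and overstate true differences between schools. All of this stands, and is why the gain is given as a range.

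**Conclusion.** The inconsistency on baseline health assessment is plain on the face of the protocol and does not depend on any analysis plan. The adjustment point holds as a readily available improvement: the formal test for anaemia does not use a school-level health baseline that the study already collects.

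Three stronger inferences are not supported:

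- **Bias.** Randomisation keeps the unadjusted estimate unbiased, and the confidence intervals are to allow for observed between-school variance.
- **A faulty sample size.** The 84 schools reproduce with no health covariate.
- **Missing consent for classes 6-7.** Section 11 describes meetings with "parents/guardians of children enrolled in standards 1-5", which might suggest this. Section 8 viii), however, seeks consent from parents or guardians at selected schools without a class limit, and the forms are in an appendix that is not shown. No conclusion can be drawn.

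The benefit is a variance reduction of about 2% to 25%, resting on ICC 0.025 and the assumed correlation and numbers above, together with protection against an imbalance whose SD is about a third of the target difference (1.7 / 5 = 0.34).

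**What to change.** 1. In sections 3, 8 i) and 10, state that health outcomes in the cohort are measured at follow-up only, and that baseline health data are school-level values from class 6-7 children who are not enrolled.
2. In section 9, specify that the anaemia and parasitaemia analyses adjust for the school's class 6-7 baseline value of the same outcome (prevalence, or mean haemoglobin for the anaemia analysis), together with the randomisation strata. The comparison of arms can remain as description but should not be the only use of these data. The unadjusted estimate can be reported alongside.

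The cost is a few sentences and one school-level covariate per health outcome. No further children, visits or samples are needed.
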